### Participant Inclusion and Exclusion Criteria

Inclusion criteria: We will include in the study men who are:

- Uncircumcised
- Aged 25 – 39 years
- Residents of the study village (has been living in the physical structure such as a compound or homestead identified during the enumeration and who has been consuming or making some contribution to food and other shared household resources).
- Intend to continue living in the village for the next 9 months, which is the estimated duration of data collection.
- Give written consent to participate in the study and the interventions.

During intervention, eligible participants will be asked to go for services with their National ID cards (if available), as well as with the referral coupon which will indicate district, Location and village of residence. Additionally, we will record participants’ three names, and last six digits of personal or friend’s telephone number. These will help in correctly identifying those who misplace their referral coupons (process described further on pg. 30). Participants who do not have a phone will be asked to give the phone number of a friend. The phone numbers and ID #s will be sorted immediately after data entry to ensure duplicates are identified, flagged such that when these participants come for services, they will be asked to describe the process of enrollment in the study to confirm they were enrolled. The RAs will ensure they at the very least mention being consented, interviewed, and asked to be physically examined to verify MC status.

Exclusion criteria: We will exclude from the study those who are;

- Circumcised
- Aged <25- or >39 years
- Non-resident of target villages
- Plans to move away from the village within nine months after enrolment
- Does not give consent to participate in the study

In addition, participants who misplace the referral card, have forgotten their Unique PIN and cannot be matched through their three names, date of birth (or age), village or phone number (matching process describe on pg. 30) will be excluded. Those who do not meet the eligibility criteria will be offered services but not included in the study.

Note: The study design and implementation is summarized in the flow chart, Fig. 3 below.

[figure not shown]

Figure 3: Schematic Presentation of study design and implementation

###

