**Inclusion/Exclusion Criteria for Baseline Phase**

Inclusion:

- Aged 25 – 39 years
- Resident of the study village - has been living in the physical structure identified during the enumeration and who has been eating together in the same household.
- Intends to continue living in the village for the next 9 months (which is the estimated duration of data collection).
- Gives written consent to participate in the study and the interventions.

Exclusion:

- Outside the age range of 25-39 years
- Non-resident of study villages
- Intends to relocate from the study village within the next 9 months
- Declines *to consent to participate in the study or the interventions*

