Recruitment Approach: Depending on participant’s availability, this phase can be conducted together with Phase 2 if the intervention tool (Appendix 6) has been approved, and done subsequent to verification of MC status; alternatively, another visit will be made if participants do not have time or if Appendix 6 has not been approved. If another visit is needed, we will visit every household with enrolled participants at a time when they are likely to be at home (with their spouses where applicable) to discuss VMMC using the demand creation tool (Appendix 16: *VMMC Demand Creation Tool kit*) as described in the next sub-section.

Participants in IPC or IPC/DSO Location will receive information on VMMC while those in DSO Locations will be informed about, and given directions to VMMC sites designated to older men. During consenting, participants will be informed that by consenting to be enrolled in the study, they are consenting to be assigned into one of the three intervention arms or control. Hence, by consenting to join the study they will also have consented to participating in the respective interventions. After delivering the intervention (whether at enrollment visit or a subsequent one), participants will be given a pre-designed referral coupon (Appendix 15: Referral Coupon) to take along when going for services. They will also be asked to memorize the serial number if possible. The RAs will be expected to return to the same households up to three times (within a period of three month) to reach those not found at home during the previous visit – this applies to both enrollment visit and the visit to deliver the intervention, if different from enrollment visit.

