4. Matching of participants enrolled in their houses with those coming for MC services:

It is important to track participants from the point of recruitment/referral to the VMMC site. We have designed a participant unique numbering system (see also pg 24 above) which makes it possible to track participants from point of referral to the VMMC site while minimizing disclosure of their identity, as described below:

- Every participant’s referral coupon will bear a pre-assigned study code that designates: Location (e.g., KAW), Village (e.g., KOD), participant’s 3 initials and an easy-to-remember six digit number which can be the last 6 digits of participant’s National ID or last six digits of his phone # or a friend’s phone # or any number (e.g. 123456). The complete code for participant Edward Albert Sungu from Kawino Location, Kodongo Village with # 123456, will therefore be: KAW/KOD/E12/A34/S56. The numbering in the Household listing form, the Tracking Log and the Referral coupons (Appendix 1, Appendix 3A and Appendix 15), will be synchronized with this numbering system to make it easier to track participants and link them to the intervention.

Additionally, the Tracking Log will also have the three names of the participant and his village, to be used in case he forgets to come with the referral coupon or does not recall the number. Thus, when a participant comes to the VMMC service site, they will be identified as follows:

1. Participants who have the referral coupon:
   - The Clinic-based RA will ask for the referral coupon (Appendix 15) given at enrolment.
   - S/he will then telephone the Data Officer based at the head office in Kisumu who maintains the Master Log in Excel (Appendix 14) and read out to the Data Officer the participant unique ID number.
   - The Data Officer will locate the Participant Unique ID number from the Master Log and tell the Clinic-based RA the three names, age, village and enrollment date of the participant, one at a time, as the clinic RA confirms with the participant.
   - If the details provided by the Data Officer match what the participant says, then he will be deemed correctly matched. Those not correctly matched will just receive circumcision services but will not be included in the study.
2. Participants who do not have the referral coupon:
   - The participant will be asked to show his national ID that should have the same number and three names recorded at enrollment. The national ID photo should resemble him.

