   - The Data Officer will search the names from the Master Log. Once found, the Clinic-based RA will ask the participant his age, village and Location. If these details match, the clinic-based RA will then ask the participant his reasons for coming to the facility. His response will reveal if the participant’s village was part of the location randomized to one of the intervention arms, and the self-reported reason(s) for coming to the site may indicate why they came (e.g., “I was told that there were special sites for older men here, so I came here” or “A person came to my house and talked to me about VMMC” etc.). During analysis, we may be able see if there are any differences by those who came with the coupon or any other information above vs. those who self-reported. If he fails to give reasons for coming and fails to describe any steps during enrolment, the participant will just receive circumcision services but will not be included in the study).

Since the Tracking Log will have identifier information (including 3 names, truncated ID number, truncated phone number, etc), we shall ensure confidentiality by locking up the log in a secure cabinet at the data office in the regional office and it will be accessible only to authorized staff, who will have signed the confidentiality agreement.

**Note**: There will be ONLY one Master Log kept at the head office in Kisumu with access limited to the Data Manager, Study Coordinator, Data Officer, 2 Statisticians and the PIs

#

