# PHASE 5: ESTABLISHING ENDLINE MC UPTAKE/ESTIMATING IMPACT OF INTERVENTIONS

At Endline, we will review our Participants Master Log (Appendix 14) to identify those who did not go for VMMC at the 45 VMMC clinics participating in the study. We will use the telephone numbers obtained during enrollment to contact the participants. Those who say that they got circumcised but are not in our Participant Master Log, we will make an appointment and visit them at home, or another convenient location, to administer consent (Appendix 2C), conduct Endline interview (**Appendix 2D: Phone and In-Person Interview with Uncircumcised Men at Endline**) and verify their circumcision status. Those who report not having gone for VMMC will be asked why they did not go, and their response recorded in Appendix 2D. If more than one reason is given, the participant will be asked to rank the top three reasons from most to least important. As enrolled participants go for VMMC services, we will be recording in the study’s Participants Master Log that they have been circumcised. However, only those who go for VMMC at study-designated clinics where we have stationed Research Assistants to monitor uptake will be recorded in the Participants Master Log. Recognizing that some participants could choose to go for circumcision in non-study clinics, we will need to capture those ones as well. To do this, we will not call any person apart from men who are listed in our Participants Master Log. We will review VMMC program theater registers in non-study clinics located within the 12 districts where the study is being conducted and compare the names with those indicated on the Participants Master Log as having not gone for VMMC. For those where the three names of VMMC clients in theater registers match the three names in the Participants Master Log, we will contact them using the phone numbers registered in the Participants Master Log and NOT in VMMC theater registers. When calling, the TASCO participants who could have been circumcised at non-study clinics will be asked if they were enrolled in the study. If they were, we will schedule a visit at home and obtain consent and if willing, conduct endline survey and verify MC status; if not, they will not be contacted further.

Inclusion/Exclusion Criteria

Inclusion:

- - 1. Was enrolled in the main study
    2. Resident of the study village
    3. Did not go for circumcision per TASCO Study database

Exclusion:

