## Data Analysis:

***Aim 1:*** ***Compare the rate of uptake of VMMC services by men aged 25-39 years exposed to Inter-Personal Communication, Designated Service Outlets, and IPC+DSO.***

The main outcome measure of this study is VMMC uptake. To assess the rate of uptake of VMMC services by uncircumcised men aged 25-39 years, we will compare the proportion of men who accept to be circumcised across the intervention arms. Specifically, the proportion of men accepting to be circumcised in each of the three arms will be compared to the proportion accepting circumcision in the no intervention group. P-values will be adjusted for multiple comparisons using the Bonferroni method. In order to take into account the clustered nature of the data, we shall also employ statistical methods suitable for analysis of cluster-randomized trials, namely the multi-level logistic regression model via the generalized estimating equations (GEE) approach with a random intercept. The random intercept term will represent the differences in true log-odds between the Locations. Odds ratio of VMMC uptake comparing intervention groups to the control group with the same underlying uptake rate will be estimated. This model will simultaneously assess individual-level and Location-level factors associated with uptake of VMMC as well as the effect of the interventions. Most importantly, it will enable the assessment of the intervention at the level at which randomization occurred: the Location level.

As outlined above under Phase 4, we shall conduct an endline survey in all households with men aged 25-39 years to establish the post-intervention MC uptake, and for those circumcised, collect information on when and where they were circumcised. These will be compared with similar data collected at baseline, using the methods described in the paragraph above. In addition, we shall extract from our database information on age of participants receiving services in each Location/Cluster. We will also have a sense of effectiveness of each recruitment strategy from surrendered referral coupons and from responses to question 1 in Appendix 20 B, asked to men who come for MC and through Appendix 2, the number of men reported and/or verified as circumcised at endline. This information, collected from multiple sources and through multiple approaches, will be compared across different arms of the study.

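### Enrolled men who come for circumcision but cannot be matched are excluded, a rule only attenders can trigger, and the endline sections conflict on who is followed up to recover them

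*Protocol*

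**What the plan says.** **Exclusion of unmatched men.** The protocol's Participant Inclusion and Exclusion Criteria exclude "participants who misplace the referral card, have forgotten their Unique PIN and cannot be matched through their three names", age, village or telephone number. The matching procedure under Activities that cut across study arms has four routes: coupon, national ID, recalled numbers, and names only. For the coupon and ID routes it states: "Those not correctly matched will just receive circumcision services but will not be included in the study". The other two routes end the same way.

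**Last matching route.** A man identified by names alone must also agree on age, village and Location, and is then asked why he came. The protocol expects the answer to show whether his village was in an intervention Location. "If he fails to give reasons for coming and fails to describe any steps during enrolment, the participant will just receive circumcision services" and is not included.

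**Coupons.** Phase 4 (Recruitment Approach) states: "After delivering the intervention (whether at enrollment visit or a subsequent one), participants will be given a pre-designed referral coupon". The matching procedure instead refers to every participant's coupon and describes it as handed out at enrolment.

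**Endline.** Phase 5 telephones men in the Master Log with no recorded circumcision. Men who say they were circumcised are visited and verified. For the others, "Those who report not having gone for VMMC will be asked why they did not go"; no physical check is described. Registers are searched in non-study clinics only, and men no longer resident in the village are excluded. The Data Analysis section says "we shall conduct an endline survey in all households with men aged 25-39 years to establish the post-intervention MC uptake". Table 8 says that men uncircumcised at baseline will be interviewed and verified in all their households.

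**The concern.** An exclusion made after enrolment should not depend on the outcome. This one does: a man who never attends a clinic is never put through matching, so he cannot fail it. Every man lost under the rule is one who attended for circumcision, and each such loss lowers recorded uptake in his arm.

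If the losses were the same in all arms, the harm would be a modest understatement of uptake. If they differed by arm, the comparison with Control would shift as well. The last matching route makes that possible, because it uses an answer expected to carry intervention content.

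The endline work is the natural safeguard, but three sections describe three different procedures. It is therefore unclear how many unmatched men would be recovered, or whether recovery would be the same in every arm.

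**Working it through.** **1. The plan's own figures.** Under Sample size Determination the protocol takes 30% v 40%, two-sided alpha 0.017, 80% power and a design effect of 2.5. The two-proportion formula gives 473 per arm. With continuity correction, 473/4 × [1 + √(1 + 4/(473 × 0.10))]² = 493. Then 493 × 2.5 = 1232.5, rounded up to 1233, which matches the protocol. The 10-point difference is the yardstick below. The protocol gives no expected rate of failed matching.

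**2. Who can be affected.** Let p be true uptake, and let u be the share of circumcised men who are unmatched at the clinic and not recovered at endline. So u = (share unmatched) × (1 − share recovered). There is no matching term for uncircumcised men.

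- Unmatched men dropped: observed = p(1 − u) / [p(1 − u) + (1 − p)]
- Unmatched men kept but logged as uncircumcised: observed = p(1 − u)

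**3. Size at p = 30%, for assumed u.**

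| u | Dropped | Counted as uncircumcised |
| --- | --- | --- |
| 5% | 0.285/0.985 = 28.9% | 28.5% |
| 10% | 0.270/0.970 = 27.8% | 27.0% |
| 15% | 0.255/0.955 = 26.7% | 25.5% |
| 20% | 0.240/0.940 = 25.5% | 24.0% |

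**4. Same u in both arms.** With u = 10% and true rates of 30% and 40%:

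- Dropped: 27.8% v 37.5%, a difference of 9.7 points. Both odds are multiplied by 0.90, so the odds ratio stays at (0.4/0.6)/(0.3/0.7) = 1.556.
- Counted as uncircumcised: 27.0% v 36.0%, a difference of 9.0 points.

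**5. Different u by arm, with no true effect (30% v 30%).** With u = 15% in Control and 5% in an intervention arm (assumed):

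- Dropped: 28.9% − 26.7% = 2.2 points.
- Counted as uncircumcised: 28.5% − 25.5% = 3.0 points.

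**6. What recovery depends on.** A man unmatched at a study clinic keeps a log entry without a circumcision, so Phase 5 would telephone him. The register search would not find him, because it covers non-study clinics only. His recovery rests on the telephone call (the number may be a friend's), his own report, and his still living in the village.

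**7. The endline sections side by side.**

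| Section | Who is followed | Who is verified |
| --- | --- | --- |
| Phase 5 | Unlogged men, by telephone; non-residents excluded | Men who claim circumcision or match a non-study register |
| Data Analysis, Aim 1 | All households with men aged 25-39 | Counts men reported and/or verified |
| Table 8 | All households with men uncircumcised at baseline | All such men |

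These give different outcome data for the same man. The two wider versions would find an unmatched man without relying on a telephone call.

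**The case against.** The strongest reply is that an unmatched man cannot literally be removed. If he cannot be linked to a log entry, his entry stays as not circumcised, he qualifies for the Phase 5 call, and he is verified if he reports circumcision. On that reading, non-inclusion means only that the clinic visit is not credited. This stands in part: misclassification is the likelier result than removal, and recovery makes u smaller than the clinic failure rate. It does not dispose of the point. Either way a success is lost unless the call succeeds, and the eligibility section still says such men are excluded.

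A second reply is that the last route need not disadvantage Control men. They reach it only after the coupon, ID and number routes fail. A man is refused only if he gives no reason and also cannot describe any enrolment step, and consent, interview and examination are the same in every arm. One of the two sample answers, a home visit about circumcision, would also fit a Control man. This stands as a limit: differential matching is possible, not shown.

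A third reply is that handling of unreached men belongs in an analysis plan. That is right, and nothing here depends on its absence. The point is the exclusion that the protocol does state.

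**Conclusion.** The point holds in limited form. The protocol contains a post-enrolment exclusion that only attenders can trigger, a last matching step that could work differently by arm, and three endline procedures that cannot all be followed. Under the assumed 5-20% unmatched and unrecovered, a true 30% reads 1 to 6 points low. An assumed 15% v 5% split between arms gives a spurious 2-3 points. The documents supply none of these rates, and at u = 0 there is no bias.

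Four stronger readings are tempting but not supported:

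- **Enrolled men leave for declining the intervention.** The criterion "Gives written consent to participate in the study and the interventions" applies at baseline. One consent covers all four arms, and men learn their arm only after enrolment.
- **Control men get no coupon.** The matching procedure gives every participant one. The sections conflict on timing, and the Control text is merely silent.
- **The 15% loss allowance takes unreached men out of the denominator.** It inflates recruitment and defines no analysis set. Even if 15% of uncircumcised men were dropped equally in both arms, 30% and 40% would read 0.30/0.895 = 33.5% and 0.40/0.910 = 44.0%. That is 10.4 points instead of 10.0, with the odds ratio still 1.556.
- **The randomised comparison is broken.** That would need a sizeable difference in u between arms, for which there is no evidence.

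**What to change.** - Delete the exclusion of unmatched men from the Participant Inclusion and Exclusion Criteria, and the matching wording that leaves them out of the study.
- State that the primary denominator is every enrolled, verified-uncircumcised man, in his Location's randomised arm, regardless of matching or follow-up. How men never reached are classified can be left to the analysis plan.
- Drop the reason for coming as a matching criterion. Rely on enrolment details that are the same in all arms.
- Keep a list of unmatched attenders so that their likely log entries are flagged for verification at endline.
- Reconcile Phase 5, Data Analysis (Aim 1) and Table 8 into one endline procedure, applied alike in all four arms. State who is contacted, how, and whose status is verified.
- Reconcile Phase 4 with the matching procedure so that coupons are given at enrolment in all arms.

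The cost is mainly wording, with slightly different stated uptake. If the wider endline survey is the one kept, Table 8 already allows about three months for it.

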### Activities that cut across study arms:

1. Intervention Delivery
   1. In all the study Locations all participants aged 25-39 years coming for circumcision will be informed about the sub-study 4 (Role of sexual partners in time to resumption of sex post-circumcision) and given informational flyer (Appendix 31).
   2. We will continue to monitor recruitment activities in all arms to document other VMMC recruitment approaches that may be provided through other channels and which may bias the results.
   3. At all study sites, comprehensive VMMC services will be provided routinely per Ministry of Health guidelines, which includes: VMMC education and risk reduction counseling, HIV testing and counseling, condom education and distribution, STI screening and treatment, and the surgical procedure.
   4. At the end of the counseling session all participants aged 25-39 years accessing VMMC services at any of our study sites will be taken through written consent process and asked one question on what/who influenced their decision to come for VMMC (Appendix 20 A: Written Consent Form with 2 Questions for MC Participants Aged 25-39 Years). The question will help to identify which messages / cadre of RA / approaches are effective in influencing decision-making for VMMC for older men. In addition, men in DSO locations going for services in non-DSO sites will be asked question 2 from the same tool (Appendix 20 B). This will help us to understand why, despite availability of DSO sites, some older men still choose to go to non-DSO sites. Information from the two questions will not be linked to the respondents; instead, the questions and possible answers will be pre-printed on a piece of paper on which staff will simply check a participant’s response and drop in a box for collection by data staff. We will run descriptive statistics to determine top actual facilitators for circumcision.
2. Monitoring of Demand Creation Activities across Study Arms

We have designed a monitoring tool (Appendix 19: Monitoring Form for Demand Creation Strategies) to document information at different stages of the study; the form will capture:

1. Questions asked by participants during delivery of the intervention
2. Any additional information given beyond what is contained in Appendix 17: ‘*All You Need to Know About VMMC*’ booklet) in DSO and Control Arms.
3. Routine recruitment for the VMMC program in all study Arms to document if similar strategies were used during the study period.
4. Matching of participants enrolled in their houses with those coming for MC services:

It is important to track participants from the point of recruitment/referral to the VMMC site. We have designed a participant unique numbering system (see also pg 24 above) which makes it possible to track participants from point of referral to the VMMC site while minimizing disclosure of their identity, as described below:

- Every participant’s referral coupon will bear a pre-assigned study code that designates: Location (e.g., KAW), Village (e.g., KOD), participant’s 3 initials and an easy-to-remember six digit number which can be the last 6 digits of participant’s National ID or last six digits of his phone # or a friend’s phone # or any number (e.g. 123456). The complete code for participant Edward Albert Sungu from Kawino Location, Kodongo Village with # 123456, will therefore be: KAW/KOD/E12/A34/S56. The numbering in the Household listing form, the Tracking Log and the Referral coupons (Appendix 1, Appendix 3A and Appendix 15), will be synchronized with this numbering system to make it easier to track participants and link them to the intervention.

Additionally, the Tracking Log will also have the three names of the participant and his village, to be used in case he forgets to come with the referral coupon or does not recall the number. Thus, when a participant comes to the VMMC service site, they will be identified as follows:

1. Participants who have the referral coupon:
   - The Clinic-based RA will ask for the referral coupon (Appendix 15) given at enrolment.
   - S/he will then telephone the Data Officer based at the head office in Kisumu who maintains the Master Log in Excel (Appendix 14) and read out to the Data Officer the participant unique ID number.
   - The Data Officer will locate the Participant Unique ID number from the Master Log and tell the Clinic-based RA the three names, age, village and enrollment date of the participant, one at a time, as the clinic RA confirms with the participant.
   - If the details provided by the Data Officer match what the participant says, then he will be deemed correctly matched. Those not correctly matched will just receive circumcision services but will not be included in the study.
2. Participants who do not have the referral coupon:
   - The participant will be asked to show his national ID that should have the same number and three names recorded at enrollment. The national ID photo should resemble him.
   - The Clinic-based RA will then telephone the Data Officer based at the head office in Kisumu and read out the participant national ID number.
   - The Data Officer will confirm if the national ID number is in the Master Log. If it exists, he will then read out to the Clinic-based RA the three names, age, village and participant unique ID number, one at a time, as the clinic RA confirms with the participant.
   - If any two of the details provided by the Data Officer match what the participant says, he will be deemed correctly matched. Those not correctly matched will just receive circumcision services but will not be included in the study.
3. Participants who do not have both referral coupon and national ID:
   - The participant will be asked if he can remember his national ID number or the cell phone number he gave during enrollment.
   - The Clinic-based RA will then telephone the Data Officer based at the head office in Kisumu and read out the participant national ID number or cell phone number.
   - The Data Officer will confirm if the national ID number or cell phone number is in the Master Log. If either exists, he will then read out to the Clinic-based RA the three names, age, village and participant unique ID number, one at a time, as the clinic-based RA confirms with the participant.
   - If any three of the details provided by the Data Officer matches what the participant says, he will be deemed correctly matched.
   - If there is no match, the participant will just receive circumcision services but will not be included in the study.
4. Participants who do not bring referral coupon or national ID number and do not remember their unique ID number, national ID number or cell phone number:
   - The participant will be asked for his three names, preferably in the order in which he gave them during enrollment.
   - The Clinic-based RA will then telephone the Data Officer based at the head office in Kisumu and give the three names of the participant.
   - The Data Officer will search the names from the Master Log. Once found, the Clinic-based RA will ask the participant his age, village and Location. If these details match, the clinic-based RA will then ask the participant his reasons for coming to the facility. His response will reveal if the participant’s village was part of the location randomized to one of the intervention arms, and the self-reported reason(s) for coming to the site may indicate why they came (e.g., “I was told that there were special sites for older men here, so I came here” or “A person came to my house and talked to me about VMMC” etc.). During analysis, we may be able see if there are any differences by those who came with the coupon or any other information above vs. those who self-reported. If he fails to give reasons for coming and fails to describe any steps during enrolment, the participant will just receive circumcision services but will not be included in the study).

Since the Tracking Log will have identifier information (including 3 names, truncated ID number, truncated phone number, etc), we shall ensure confidentiality by locking up the log in a secure cabinet at the data office in the regional office and it will be accessible only to authorized staff, who will have signed the confidentiality agreement.

**Note**: There will be ONLY one Master Log kept at the head office in Kisumu with access limited to the Data Manager, Study Coordinator, Data Officer, 2 Statisticians and the PIs

#

